**6. Methods:**

a) Subject Numbers: How many local subjects? 150

How many total subjects? 150

b) Major Inclusion/Exclusion Criteria:

Patients 18- 74 years referred to the Forzani Colorectal Cancer Screening Centre in Calgary, Alberta, Canada for colonoscopy will be considered. Major exclusion criteria will be acute coronary syndrome, congestive heart failure, unstable angina, known or suspected renal failure, ascites, megacolon, known or suspected bowel obstruction, or other comorbidities that may prevent colonoscopy as well as previous partial or subtotal colectomy or if the colonoscopy is warranted for the evaluation of diarrhea.

c) Interventions (What will be done to the subjects and for how long?)

Patients will be allocated to one of two groups: (1) oral Pico-Salax (two sachets, with 1.5-2L of water following each sachet) with Dulcolax (Bisacodyl, 4 tablets); (2) split dose Polyethylene Glycol-Based Lavage (2L + 2L). Specific instructions will be provided on preparation timing, depending on whether colonoscopy is prior to 10AM or after 10AM. Further instructions are given to participants regarding diet in the days leading up to their procedure (see appendix).

d) Primary Outcome Variables (Briefly describe what will be measured and how/using what measurement tools)

The previously validated Ottawa bowel preparation scale will be used to assess the quality of bowel cleanliness. Each of the right, mid and rectosigmoid colon is rated on a 5-point scale (0-4). In addition, a complete 3-point rating for overall colonic fluid is assessed resulting in an overall score range of 0 to 14. An excellent preparation with little fluid would score 0 to 1; a good preparation, 2 to 4; while scores higher than 4 would indicate progressively worsening bowel preparations. A completely unprepared colon would score 11 to 14, depending on the amount of colonic fluid. Additionally a simplified overall cleanliness score will be utilized and compared to the Ottawa scale as a gold standard (both included in an appendix).

e) Limitations (please list briefly any limitations you have identified in the study)

**APPLICATION FOR SCIENTIFIC, ADMINISTRATIVE &  
ETHICAL REVIEW OF HUMAN SUBJECT CLINICAL TRIALS  
AND HUMAN SUBJECT HEALTH RESEARCH**

("Human Subject" includes human biosamples, tissue and genetic information as well as people)

**7. Statistical Considerations in the study design:**

- a) What is your sample size and how do you justify it? (Provide details of sample size calculation).

In our previous study at CCSC utilizing the Ottawa Prep score, we observed an effect size for segment scores that ranged from 0.5 to 1.0 (moderate) with a standard deviation of 1.02. For a two group ANOVA a total sample size of size of 130 patients will be required for a two tailed alpha at 0.05 and an 80% power. Based on the experience from our previous study, an additional 15%, or 20 patients, will be added to the total sample size to account for early withdrawals and incomplete colonoscopies.

- b) Data Analysis (Which method of analysis will you use?)

Descriptive statistics will be used for baseline characteristics. The Ottawa bowel prep scale produces data that is approximately normally distributed. Two group ANOVA will be used to assess for the presence of group differences in the prep scores between groups. The influence of colonoscopy time (AM vs PM) will be assessed by entering scope time as a factor in the ANOVA Model. The secondary endpoints of tolerability will be assessed using the Mann Whitney U test. A sub project will be to assess the agreement between the Ottawa Scale (validated gold standard) and the simplified overall score.

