As an alternative, recent research has explored low-volume or split dose PEG preparations, sometimes with the addition of a stimulant laxative, in order to circumvent the issues surrounding preparation adherence in 4L doses, with positive results in regards to efficacy and tolerability. Low-volume PEG plus ascorbic acid was as effective as a high-volume PEG plus electrolytes preparation, but had superior palatability. In a recent study conducted here at the Colon Cancer Screening Centre, a split dose (2L+2L) of Colyte, a PEG preparation, was found to provide a cleaner colon with less residual fluid than a one-time 4L dose of the same preparation, in both morning and afternoon procedures, although the best effect was seen when the last dose preceded the procedure by at least 5 hours. Timing of split dose application has been outlined as an important factor in optimizing bowel cleansing and colon visualization.

Pico-Salax (Sodium Picosulphate and Magnesium citrate) is a low-volume bowel preparation available in Canada. Evidence suggests that sodium picosulphate plus magnesium citrate bowel preparations, such as Pico-Salax, consistently yielded a high efficacy rating for colon cleansing has been found to be at least as effective as PEG bowel preparations, and may be much better tolerated, with fewer side effects. The addition of stimulant and osmotic laxatives to bowel preparations has shown increased efficacy in bowel cleansing. In a recent study by Hookey, L. et al (2009), Pico-Salax plus a two-day dose of Bisacodyl was found to provide superior colon cleansing in the right colon compared to Pico-Salax alone and NaP, and was found to be significantly better tolerated by patients than NaP. This is clinically significant as flat lesions are relatively more frequent in the right colon, and bowel preparation is often the poorest in this region. The addition of Bisacodyl did not negatively affect the safety profile of Pico-Salax as a preparation. There is a lack of research on split dose Pico-Salax preparations; this study will examine the effect of splitting Pico-Salax dosing overnight in patients whose colonoscopy is occurring after 10AM.

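### The arm comparison omits the preparation schedule, and the planned AM/PM factor does not match the 10AM cut that defines that schedule; one additive arm-plus-schedule ANOVA would be a nearly free improvement

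*Protocol*

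**What the plan says.** Protocol, Section C, item 7b (Data Analysis) assigns the arm comparison to an unadjusted test: "Two group ANOVA will be used to assess for the presence of group differences in the prep scores between groups". The next sentence brings in time of day for a different purpose: "The influence of colonoscopy time (AM vs PM) will be assessed by entering scope time as a factor in the ANOVA Model". Item 7b does not say whether that second model contains an arm-by-time term.

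Item 7a sizes the trial on the unadjusted test: "For a two group ANOVA a total sample size of size of 130 patients will be required", at the conventional two-sided 5% level and 80% power. Its inputs are given as "we observed an effect size for segment scores that ranged from 0.5 to 1.0 (moderate) with a standard deviation of 1.02".

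Two other places bear on timing:

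- Section C, item 3 (Background Rationale) says "Timing of split dose application has been outlined as an important factor in optimizing bowel cleansing and colon visualization", and later that "this study will examine the effect of splitting Pico-Salax dosing overnight in patients whose colonoscopy is occurring after 10AM".
- Section C, item 6c (Interventions) makes the preparation-timing instructions depend on whether the colonoscopy is before or after 10AM.

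**The concern.** There are two linked problems.

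The first is a mismatch of cut points. The instructions and the stated after-10AM question divide patients at 10AM, whereas the analysis factor divides them into AM and PM. If AM means before noon, as it ordinarily does, a patient scoped between 10AM and noon follows the after-10AM schedule but is analysed with the before-10AM patients. The factor then mixes two schedules in its AM level. In addition, neither sentence of item 7b names an arm difference among after-10AM patients, although the Background says that group will be examined.

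The second is efficiency. The protocol already plans to use scope time as a factor and treats dose timing as important for cleansing. Yet the model named for the arm comparison leaves any such variation in the error term. If schedule affects the score, an additive adjustment narrows the confidence interval for the arm difference without adding patients. Fixing one model in advance also closes off a choice between two arm p-values for the same outcome.

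**Working it through.** **Inputs from the Protocol, Section C, item 7a.** Two-sided alpha 0.05; power 80%; SD 1.02 for segment scores; effect 0.5 to 1.0; 130 evaluable patients.

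**Assumptions.** Allocation is 1:1, so 65 per arm (the ratio is not stated). The difference is 0.5 points, the lower end of the range. Patients split 50:50 between schedule groups. The scope-time effect is not given, so a range is shown. The figures apply to segment scores, because that is what the SD of 1.02 describes.

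**1. Reproducing the 130.** The normal approximation is n per arm = 2(1.960 + 0.842)² × SD² / difference².

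- Difference 0.5, SD 1.02: 2 × 7.85 × 1.0404 / 0.25 = 65.3, so 66 per arm and 132 in total (134 by the t-test).
- Standardised effect 0.5: 126 in total (128 by the t-test).
- An effect of 1.0 needs only 32 to 36 in total.

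The stated 130 therefore reproduces closely, rests on 0.5, and involves no adjustment for scope time.

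**2. Unadjusted power with 130.** The noncentrality is 0.5 / (1.02 × √(2/65)) = 2.79. On 128 df this gives 79.2%.

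**3. Adjusted power.** With an even split, a shift of s points between schedule groups explains R² = 0.25 s² / 1.02² of the variance. The residual SD is 1.02 × √(1 − R²), on 127 df.

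| Assumed shift s | R² | Residual SD | Power, adjusted |
|---|---|---|---|
| 0 | 0 | 1.020 | 79.2% |
| 0.25 | 1.5% | 1.012 | 79.8% |
| 0.5 | 6.0% | 0.989 | 81.6% |
| 0.75 | 13.5% | 0.949 | 84.7% |

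The lost degree of freedom costs less than 0.1 percentage point. Chance imbalance of schedule between arms adds a little more: at no scope-time effect, simulated power is 79.1% adjusted against 79.5% unadjusted.

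**4. Choosing the smaller of two p-values.** In simulated null trials (n = 130, even split), reporting whichever of the unadjusted and additive p-values is smaller gives a type I error of about 5.4% with no scope-time effect, rising to about 6.7% at a shift of 0.75. The two tests are highly correlated, so the figure stays well below the 9.75% of two independent tests. Either model alone holds 5%.

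**5. What can be estimated by schedule.** Approximate 95% CI half-widths are:

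- Arm difference overall: 1.96 × 1.02 × √(4/130) = 0.35.
- Arm difference within one schedule group of 65: 1.96 × 1.02 × √(8/130) = 0.50.
- Arm-by-schedule interaction: 1.96 × 1.02 × √(16/130) = 0.70.

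The within-group half-width equals the whole difference the trial is sized on, so the schedule-specific results can only be estimates.

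**The case against.** The strongest reply is that item 7b contains no error. An unadjusted comparison in a randomised trial is valid, and covariates and sensitivity analyses are commonly settled in a SAP, which is not at hand. That stands, and it is why the point is a minor improvement. It does not dispose of the mismatch between AM/PM and 10AM, which lies within the protocol's own text.

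Three stronger readings are tempting but not supported.

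- A reader might infer that two models compete and neither is decisive. The plain reading is otherwise: the two-group ANOVA is given the arm comparison and the sample size is built on it, while the scope-time model has a different stated purpose. The inflation to at most about 6.7% arises only if someone substitutes a p-value that the protocol does not assign to the arm comparison.
- A reader might infer that the plan is losing power. The 130 was calculated without adjustment, so nothing is lost against the plan. Any gain depends on a scope-time effect the documents do not report; it is nil if there is none, and 0.6 percentage points for a 0.25-point shift.
- A reader might take the Background as showing that AM vs PM is a known source of variation. Its sentence concerns when the doses are taken. Scope time may act through that, but the documents do not quantify it.

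It is also fair to say that adjustment is nearly free only in additive form. If the arm effect were instead an equally weighted average from an interaction model with an assumed 30/70 split, simulated power would fall to about 71% at R² 0, 73% at 0.05 and 75% at 0.10. Since item 7b does not exclude an interaction, the form of the model should be stated.

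**Conclusion.** The point holds as a minor, nearly free improvement. The AM/PM analysis factor does not correspond to the 10AM cut that determines the preparation schedule, and item 7b names no arm difference for the after-10AM patients the Background singles out. Reading the arm effect from one additive arm-plus-schedule model would raise power from 79.2% to between 79.2% and 84.7%, over assumed shifts of 0 to 0.75 points with an even split, 130 evaluable patients, a difference of 0.5 and an SD of 1.02. It would also rule out choosing between two p-values. The planned unadjusted test remains valid and the sample size does not change.

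**What to change.** In Section C, item 7b:

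1. State that, for each prep-score outcome, the arm effect is read from one additive ANOVA with arm and schedule, with no interaction term in that model.
2. Define schedule as the appointment before vs after 10AM, using the appointment time fixed before randomisation and not the time the procedure actually took place. Reconcile the AM/PM wording with the 10AM cut in item 6c and the Background.
3. Keep the unadjusted two-group ANOVA as a labelled sensitivity analysis.
4. Report the arm difference with its 95% CI in each schedule group, described as an estimate and not a decisive test (half-width about 0.50 under an even split, wider in the smaller group otherwise).

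The cost is a few sentences, one degree of freedom and a slightly longer results table. No extra patients are needed; scope time is already a planned factor, and the appointment time has to be known in order to give the right instructions.

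### The ANOVA splits scope time at AM vs PM, but the preparation instructions change at 10AM, so the planned timing factor does not match the two schedules given

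*Protocol*

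**What the plan says.** Three places in Section C of the protocol bear on this.

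- **Item 6, Methods, c) Interventions:** "Specific instructions will be provided on preparation timing, depending on whether colonoscopy is prior to 10AM or after 10AM".
- **Item 3, Background Rationale:** after noting how little is known about split-dose Pico-Salax, it says "this study will examine the effect of splitting Pico-Salax dosing overnight in patients whose colonoscopy is occurring after 10AM".
- **Item 7, Statistical Considerations, b) Data Analysis:** "Two group ANOVA will be used to assess for the presence of group differences in the prep scores between groups", followed by "The influence of colonoscopy time (AM vs PM) will be assessed by entering scope time as a factor in the ANOVA Model".

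No text equates AM with before 10AM, and this is the only timing factor the protocol names. Item 4 (Objectives) lists no timing or schedule effect among the primary or secondary outcomes.

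**The concern.** The cut-off that decides how a patient prepares is 10AM. The cut-off in the model, on its ordinary meaning, is noon. Between the two lies a group that prepares like the PM patients and is analysed with the early-morning patients, so the AM level mixes two sets of instructions.

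The protocol itself treats timing as important. Its background cites the timing of split doses as a factor in cleansing, and reports that the centre's previous study did best when at least 5 hours separated the last dose from the procedure. A factor that pools two schedules gives a diluted answer about schedule, and it does not separate the after-10AM patients whom the background singles out.

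**Working it through.** **1. The plan's own figure.** Item 7 gives an "effect size for segment scores that ranged from 0.5 to 1.0 (moderate) with a standard deviation of 1.02" and a "total sample size of size of 130 patients will be required for a two tailed alpha at 0.05 and an 80% power". Assuming 1:1 allocation and a 0.5-point difference with SD 1.02:

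n per arm = 2 × (1.960 + 0.842)² × 1.02² / 0.5² ≈ 65.3, rounded up to 66, total 132.

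Taking 0.5 as a standardised effect with a t-test gives 128. The stated 130 lies between and is reproduced to within 3%. Adding 15% gives 130 × 1.15 = 149.5, or about 150. Nothing below changes this.

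**2. Dilution of the schedule contrast.** Let a be the share scoped before 10AM, b the share from 10AM to noon, and c the share in the PM. Let μ_B and μ_A be the mean scores under the before-10AM and after-10AM instructions, with no other time-of-day effect.

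- AM mean = (a·μ_B + b·μ_A)/(a + b)
- PM mean = μ_A
- AM − PM = [a/(a + b)] × (μ_B − μ_A)

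**3. Size over an assumed range.** The protocol gives no clinic hours or slot shares, so a, b and c are assumptions, with c fixed at 50%. Power is for a 0.5-point schedule difference that is the same in both arms, SD 1.02, 130 analysed, two-sided 0.05, normal approximation. The small extra variance from mixing schedules within AM is ignored.

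| a / b / c | 10AM-noon patients, of 150 | Share of contrast recovered | Power, 10AM split | Power, AM vs PM |
|---|---|---|---|---|
| 40 / 10 / 50% | 15 | 0.40/0.50 = 80% | 78% | 61% |
| 30 / 20 / 50% | 30 | 0.30/0.50 = 60% | 73% | 39% |
| 20 / 30 / 50% | 45 | 0.20/0.50 = 40% | 61% | 20% |

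For the middle row, the 10AM split compares 39 with 91 patients: SE = 1.02 × √(1/39 + 1/91) = 0.195, and 0.5/0.195 = 2.56. AM vs PM compares 65 with 65 for a diluted 0.3 points: SE = 1.02 × √(2/65) = 0.179, and 0.3/0.179 = 1.68.

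**4. The arm comparison.** A simulation of 4,000 trials used 65 patients per arm, shares of 30/20/50%, a 0.5-point schedule difference and no arm-by-schedule interaction. With a true arm effect of 0.5 the mean estimate was 0.498 under both codings. Power was 78.7% with the 10AM factor and 77.4% with AM vs PM. With no arm effect, type I error was 4.8% and 5.2%.

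**5. An arm-by-schedule term.** For a 0.5-point interaction with 130 analysed:

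- 50/50 slot split: four cells of 32.5, SE = 1.02 × √(4/32.5) = 0.358, power about 29%.
- 25/75 split: two cells of 16.25 and two of 48.75, SE = 1.02 × √(2/16.25 + 2/48.75) = 0.413, power about 23%.

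**The case against.** The strongest reply is that the factor is labelled colonoscopy time, not schedule. On that label an 11AM scope is correctly coded AM. AM vs PM also has a precedent, since the background describes the centre's earlier study in terms of morning and afternoon procedures. The phrase may even be loose shorthand for the 10AM cut-off. The sentence about overnight splitting stands in the background and not in the objectives, and it can be read as describing how Pico-Salax is given rather than as announcing a before/after-10AM comparison.

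Most of this stands, and it limits the point. A reader might infer that patients are misclassified outright. The text does not support that: they are pooled with patients on other instructions, which matters only if the factor is meant to inform on schedule. A reader might also infer that scope times drift after randomisation and so corrupt the factor. The protocol does not say whether scope time is actual or scheduled, so that is conjecture.

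The reply does not remove the mismatch. The protocol fixes the factor at one cut-off and the instructions at another, and nothing in it reconciles them. If AM vs PM is shorthand, the text needs to say so.

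**Conclusion.** The mismatch is real, and its severity is minor to moderate. As worded, the timing factor recovers a/(a+b) of any difference between the two schedules: 80% to 40% over the range shown. That range rests on assumed slot shares and on there being no other time-of-day effect. If few scopes fall between 10AM and noon, the loss is small.

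A reader might go further and conclude that the treatment comparison is biased or that the trial is too small. Neither follows. The simulated arm effect is the same under both codings, power and type I error barely move, and the 130 is reproduced. Nor do the documents support calling an arm-by-schedule interaction mandatory: the protocol plans none, and power for one of 0.5 points is only about 23% to 29%.

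**What to change.** In item 7 b), replace the AM vs PM factor with wording such as:

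> *Timing will be entered as a two-level factor defined by the preparation-timing instruction the patient was given (before 10AM or after 10AM). The level to which a 10AM appointment belongs will be stated.*

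The last clause is needed because the methods speak only of before and after 10AM. AM vs PM may stay as a descriptive factor. If the authors want to know whether the schedule difference varies by arm, an arm-by-schedule term can be reported as exploratory, with its low power acknowledged.

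The cost is a sentence or two and one recorded field. The study assistant instructs each patient and the instructions depend on the slot, so the level should be known when the patient is instructed. The planned sample size does not change, and no change to dosing or timing is proposed.

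One limitation remains. Schedule follows the appointment and is not randomised, so a before/after-10AM contrast is still confounded with time of day and must be reported as observational.

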**5. Basic Study Design (Briefly describe your study):**

All patients between the ages of 18 to 74 years referred to the Forzani Colorectal Cancer Screening Centre in Calgary, Alberta, Canada for colonoscopy will be considered for inclusion. During pre-assessments at the clinic, patients are asked to consider a general research consent. If they agree to that, then they will be approached for consideration of participating in this study and presented with an "Invitation to Participate in a Research Study" form (appendix); the study assistant will obtain final consent if they agree. Those not interested in participating will simply receive their physician's standard bowel preparation protocol. There will be no coercion of any sort. Enrollment of participants will be performed with block randomizations of 8 by using a computer-generated table, with allocation concealment maintained through the use of consecutively numbered sealed envelopes.

Colonoscopists and investigators will be blinded to allocation groups. Patients will be allocated to one of two groups: (1) oral Pico-Salax (two sachets, with 1.5-2L of water following each sachet) with Dulcolax (Bisacodyl, 4 tablets); (2) split dose Polyethylene Glycol-Based Lavage (2L + 2L).

A study assistant will assign patients to their group and instruct them on the proper use of their assigned bowel preparation method. Patients will be given a tolerability questionnaire, which has been modified from a previously used questionnaire, to be completed once their bowel preparation is finished and before coming to the Centre for the colonoscopy (included in the appendix). Patient concerns or questions regarding the preparation will be directed toward the study assistant or clinic nurses as opposed to their endoscopist, so as to avoid unblinding the endoscopist.

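### Tolerability is compared with a valid but unstratified Mann-Whitney U test, although the schedule patients rate changes at 10AM; stratifying by that band is a cheap, optional gain

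*Protocol*

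**What the plan says.** Section 7b names one test for the patient-reported endpoints: "The secondary endpoints of tolerability will be assessed using the Mann Whitney U test". It attaches no scope-time term or stratum to that test. For the cleanliness scores, the same paragraph does bring in scope time: "The influence of colonoscopy time (AM vs PM) will be assessed by entering scope time as a factor in the ANOVA Model".

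Section 6c ties the timetable to a clock cut: "Specific instructions will be provided on preparation timing, depending on whether colonoscopy is prior to 10AM or after 10AM". The Background Rationale adds, for one arm, that "this study will examine the effect of splitting Pico-Salax dosing overnight in patients whose colonoscopy is occurring after 10AM".

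On allocation, Section 5 says "Enrollment of participants will be performed with block randomizations of 8 by using a computer-generated table" and mentions no stratification by scope time. Section 4 lists satisfaction among the primary outcomes, and preparation duration and discomfort as secondary.

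**The concern.** Tolerability is a rating of the preparation itself, and the timetable of that preparation differs between patients scoped before and after 10AM. If one timetable is harder to bear whichever product is taken, the pooled ranks carry variation that has nothing to do with treatment. Because allocation is not stated to be balanced within bands, a chance imbalance would also go unadjusted. A rank test that compares patients only within their own band removes both.

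What is at stake is power, not validity. The information needed is already in the trial: the band decides which instructions a patient receives, and scope time is needed for the planned ANOVA.

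**Working it through.** **The plan's own figure.** Section 7a reports that "we observed an effect size for segment scores that ranged from 0.5 to 1.0 (moderate) with a standard deviation of 1.02" and concludes that "a total sample size of size of 130 patients will be required for a two tailed alpha at 0.05 and an 80% power". Reading 0.5 as a raw difference with SD 1.02, the normal approximation gives n per arm = 2 × (1.960 + 0.842)² × (1.02/0.5)² = 2 × 7.85 × 4.16 ≈ 65.3, so 66 per arm and 132 in total. Reading 0.5 as a standardised effect, the t-test gives 128. The stated 130 is therefore reproduced. Adding 15% gives 130 × 1.15 = 149.5, or 150. All of this concerns Ottawa segment scores; the protocol gives no effect size, SD or power for tolerability.

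**Inputs to the comparison.**
- From the protocol: 130 evaluable patients, two arms, two-sided 5% level, allocation not stratified by band.
- Assumed: 1:1 allocation; a five-level item cut from a normal latent score; a treatment effect of 0.49 SD (0.5/1.02, borrowed from the Ottawa figures); an additive schedule shift of 0 to 1.0 SD, the same in both arms; half, or 30%, of patients in one band.

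**Statistics.** The Mann-Whitney test uses the treated-arm rank sum over all patients. The van Elteren test ranks within each band k and uses T = Σ R_k/(N_k + 1), where R_k is the treated-arm rank sum in band k and N_k the band size. Its null mean is Σ n_1k/2, with n_1k the treated patients in that band, and its variance is the tie-corrected permutation variance summed over bands. Each case had 4,000 runs. The simulation error of a single power figure is about √(0.70 × 0.30/4000) = 0.7 points.

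**Power, shift common to both arms.**

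| Schedule shift (SD) | 50/50 bands: unstratified | Stratified | Gain (points) | 30/70 bands: gain (points) |
|---|---|---|---|---|
| 0 | 73.1% | 72.7% | −0.4 | −0.6 |
| 0.2 | 73.7% | 73.4% | −0.3 | 0.1 |
| 0.5 | 69.3% | 70.8% | 1.5 | 1.5 |
| 0.8 | 64.4% | 69.3% | 4.9 | 3.7 |
| 1.0 | 58.3% | 67.1% | 8.8 | 6.5 |

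Only the gap between the two tests is due to pooling. The stratified column also falls, because a large shift piles patients into the end category of a five-level item, and no test recovers that.

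A separate simulation with a 0.5 SD treatment effect and equal bands gave 75.7% v 75.6% with no shift, 74.2% v 76.1% at 0.5 SD, 70.2% v 75.7% at 0.8 SD and 67.0% v 76.0% at 1.0 SD. Those are gains of −0.1, 1.9, 5.5 and 9.0 points. Absolute power moves with the assumptions; the gain hardly does.

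**Type I error.** With no treatment effect, both tests rejected in about 4.3% to 5.5% of runs, whatever the schedule shift.

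**Shift in one arm only.** When the schedule shift is added to a single arm, the two tests differ by no more than about 1 point, with no gain worth having. The shift is then a treatment-by-schedule interaction, and the stratified test averages over it just as the pooled one does.

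**The case against.** The strongest reply is that nothing here is wrong. Mann-Whitney suits an ordinal questionnaire, it holds its level, and stratifying it is a detail that a SAP could add. That stands, and it is why the point is offered only as an improvement.

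The harm is also hypothetical. No passage says that the schedule affects tolerability, the questionnaire's scale and the share of patients in each band are not given, and the detailed timing instructions are in an appendix not shown. A material loss needs a shift of 0.8 SD or more, larger than the treatment effect assumed. The base of 130 may be pessimistic too, since the questionnaire is completed before the patient attends and incomplete colonoscopies need not lose it.

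Four stronger readings might be inferred, and the protocol does not support them:
- **That pooling definitely weakens the comparison.** This needs a shift common to both arms, which is not documented. The Background sentence describes a change in one arm, the case in which stratifying gains nothing.
- **That Pico-Salax is split overnight only after 10AM.** The sentence says that the effect of splitting will be examined in those patients; the exclusivity is an inference.
- **That leaving out scope time contradicts the ANOVA.** The stated purpose there is to assess the influence of time, not to gain precision, and the factor is AM v PM rather than the 10AM cut.
- **That a primary outcome loses power.** The quoted sentence covers secondary tolerability endpoints. Whether it also governs satisfaction, which Section 4 ranks as primary, is unclear.

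**Conclusion.** The choice is valid but leaves a possible gain unused. With 130 patients, 1:1 allocation and a schedule shift acting equally in both arms, the pooled test gives up about 0 to 2 points of power for shifts of 0.5 SD or less, 4 to 6 at 0.8 SD and 6 to 9 at 1.0 SD. The lower ends of the last two ranges come from uneven bands. Every shift is an assumption, so these are conditional sizes, not an estimate of what the trial will lose. The case for changing rests on the asymmetry: a possible gain of several points against a cost of under 1 point if schedule has no effect, or about 1 point if it acts in one arm only.

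**What to change.** In Section 7b, replace the Mann-Whitney sentence with wording such as: *Tolerability outcomes will be compared between groups with a Wilcoxon rank-sum test stratified by scheduled colonoscopy band, before or after 10AM (van Elteren test); results will also be shown by band.*

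- Define the band by the scheduled time, fixed before randomisation where available, rather than the actual start. Place a 10AM booking in the band whose instructions that patient receives.
- Use the 10AM cut, not AM v PM, because 10AM is where the schedule changes.
- Report each band's results, because the stratified test averages over any treatment-by-schedule interaction and will not reveal it.
- Apply the same test to satisfaction if it is analysed with the tolerability questionnaire.

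The cost is one sentence settled before the data are seen. No extra patients or data items are needed.
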